### Outcomes

Our primary objective is to observe breast tumor recurrence, including ipsilateral, regional, contralateral, and distant recurrences of breast cancer (DCIS or invasive cancer events).

Our secondary objective is to assess overall survival in all patients, adverse effects of RT and tamoxifen, and translational studies—including single nucleotide polymorphisms (SNPs), extracellular matrix (ECM)- and immune-related molecules, and mutational analyses of selected genes.

### Translational studies

Pathologically, tumor cells of DCIS are surrounded by a dynamic layer of ECM, including myoepithelial cells (MECs), basement membranes, immune cells, fibroblasts, and stroma [18]. These molecules within the microenvironments of DCIS may participate in the progression of DCIS to invasive ductal carcinoma (IDC) or enhance DCIS cells to migrate, thus causing recurrence and metastases [18]. MECs can upregulate the expression of tumor suppressor proteins, such as maspin, avβ6, MMP8, and TIMP-1, and may drive progression of DCIS to IDC tumor cells [19, 20].　We also showed that stromal CD10 (a cell surface zinc-dependent metalloproteinase [21]) expression (*P* = 0.024) and loss of a tumor suppressor gene retinoblastoma (RB) [22] expression (*P* = 0.01) were closely associated with a higher incidence of IBTR in breast DCIS through multivariate analyses [23].

Regarding studies on the role of immune cells in the biology of breast DCIS [24], Hendry et al. reported that tumor infiltrating lymphocytes (TILs) were significantly greater in high-grade, ER-negative, and HER2-positive tumors of DCIS [25]. Furthermore, the TIL score was significantly higher in cases with *TP53* mutations [25]. The authors also found that the positive rate for programmed death-ligand 1 (PD-L1) was rarely present in tumor parts (11%) when compared with immune cell parts (67%) [25]. Interestingly, PD-L1 expression found in any part of tumor or immune cells was significantly associated with ER-negative and HER2-positive status in breast DCIS [25]. However, Thompson et al. showed that none of the DCIS cells expressed PD-L1, but most of the DCIS-surrounding infiltrating lymphocytes expressed PD-L1 [26].

To evaluate the association between breast cancer susceptibility loci and the risk of DCIS, Campa et al. genotyped 39 SNPs correlated with the risk of invasive breast cancers in three groups, including 1,317 cases of breast DCIS, 10,645 cases of invasive breast cancer, and 14,006 healthy controls [27]. They showed that five SNPs of *CDKN2BAS*_rs1011970, *FGFR2*_rs3750817, *FGFR2*_rs2981582, *TNRC9*_rs3803662, and 5p12_rs10941679 were closely correlated with the development of breast DCIS (*P* < 0.0016) [27]. Previously, we reported that *MAP3K1*_rs889312 (C/C) significantly correlated with a worse prognosis in patients with early-stage breast cancer who received adjuvant hormonal therapy alone (no chemotherapy) [28]. In addition, mutated *MAP3K1* was found in tumor cells of synchronous DCIS with IDC [29, 30]. In breast DCIS cases, we found that *MAP3K1* expression was closely associated with a higher 7-year IBTR rate (36.8% vs. 14.3%, *P* = 0.015) [23]. Furthermore, we showed that inhibition of *MAP3K1* significantly reduced cell growth and migration and NF-κB-dependent genes; it also enhanced the cytotoxicity of tamoxifen in two ER-positive IDC cell lines (MCF-7 and T-47D*,* to mimic DCIS) [31].

Based on the aforementioned results, we will explore which biomarkers are associated with local recurrence of DCIS. The translation studies will be divided into three parts: (1) SNPs analysis (DNA extracted from mononuclear cells obtained from peripheral blood)—including *CDKN2BAS*_rs1011970, *FGFR2*_rs3750817, *FGFR2*_rs2981582, *TNRC9*_rs3803662, 5p12_rs10941679, *CYP2B6*_rs3211371, and *MAP3K1*_rs889312—will be performed in all patients who agree to participate in the translational study; (2) the expression pattern of ECM-related molecules—including CD10, MAP3K1, retinoblastoma, maspin, αvβ6, MMP-8, MMP-9, TIMP-1, TGF-β—and immune cell-related molecules—including CD4, CD8, regulatory T cells (FoxP3 +), PD-L1, macrophages, and myeloid-derived suppressor cells *(*MDSC)—will be assessed by immunohistochemical staining in recurrent cases and in selected matched non-recurrent controls; and (3) mutations in genes such as *TP53, PIK3CA, GATA3, MLL3, and MAP3K1* in DNA extracted from paraffin-embedded tissue specimens will be analyzed to understand the relationship between the expression of these genes and clinical outcomes in patients.

### Participant timeline

The participant timeline is presented in Table 1. Clinical assessments, including physical examinations and adverse events resulting from RT or low-dose tamoxifen, will be recorded in a case report form. During the follow-up period, participants will undergo breast ultrasound, mammography, and chest radiography annually.

**Table 1 Tab1:** Participant timeline

	**Study Period of Non-inferiority trial**							
**Characteristics**	Enrollment	Allocation	Post Allocation					
Time point	-6 weeks	0	0–3 months	6 months	9 months	12 months	Within 2–5 years	5–10 years
Enrollment:								
Eligibility screen	V							
Informed consent	V							
Randomization	V							
Allocation		V						
Interventions:								
Radiotherapy			V					
Tamoxifen			V					
Assessments:								
Physical examination	V		V	V	V	V	Every 3 months	Every 6 months
KPS	V		V	V	V	V	Every 3 months	Every 6 months
Complete blood count	V		V		V		Every 6 months	Annually
Serum biochemistry	V		V		V		Every 6 months	Annually
Adverse events			V	V	V	V	Every 3 months	Every 6 months
Breast ultrasound^a^				V			Annually	Annually
Mammography^a^					V		Annually	Annually
Chest X-ray						V	Annually	Annually

*Abbreviation*: *KPS* Karnofsky performance score

^a^based on the BIRADS score, if BIRADS 3, suggestion, follow-up every 6 months

### Sample size

This study is designed to evaluate whether the efficacy of low-dose tamoxifen in reducing IBTR is not inferior to that of whole breast irradiation in patients with low-risk and ER-positive breast DCIS. We hypothesize that in all patients who meet the cohort 1 criteria of the ECOG E5194 study and have ER-positive status in the tumor, the 7-year IBTR rate in those who underwent BCS alone will be < 10.5% (assumption: 6–7%). In our previous study, breast DCIS patients who underwent BCS alone had the ECOG E5194 cohort 1 criteria, in whom the 7-year IBTR rate was 5% and 8% in the ER-positive and ER-negative groups, respectively [7]. For the ER-positive group tumors, most patients received tamoxifen as an adjuvant setting. Under these assumptions, we hypothesized that for low-risk breast DCIS, the 7-year IBTR rate would be approximately 6% in patients who underwent BCS alone (neither tamoxifen nor RT). The current trial was designed to evaluate whether the administration of low-dose tamoxifen (tamoxifen 5 mg for 5 years; experimental group) is not inferior in decreasing the cumulative incidence of IBTR when compared with the prescription of RT (50 Gy in 25 fractions or 40.05 Gy in 15 fractions; control group). We assume that a 6% incidence of IBTR at 7 years will be observed in participants who underwent whole breast RT alone and expect that the cumulative incidence of 7-year IBTR will not be > 6% in participants who receive low-dose tamoxifen (5 mg for 5 years).

In total, 385 patients are needed in each group to provide 90% β-power with an α type I error of 5% (margin, IBTR difference, 5%); this permits a loss of 5% of patients due to follow-up at 5 years (statistical methods are shown in Table 2). As approximately 5% of patients cannot tolerate the side effects of low-dose tamoxifen and will receive RT, we estimate that 405 patients will be enrolled in the tamoxifen arm. Therefore, 810 patients will be enrolled in this randomized non-inferiority trial. The targeted number of breast events is not described in the protocol, but the ripeness of the data from this trial will be revaluated and deliberated by Taiwanese and Japanese teams. If at least 80% of case report forms are returned 5 years after starting treatment, we will properly consolidate this trial’s corrected data.

**Table 2 Tab2:** Statistical methods

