**α: type 1 error—> 0.05**
**β: power—> 0.9**
**Assume (no-RT) low risk IBTR: 6%**
**Assume that Tamoxifen = RT = 6%**
**Assume a margin (IBTR difference: 5%)**
**N = (Z**_**α**_** + Z**_**β**_**)**^**2**^**xS**^**2**^**/Δ**^**2**^ = **385 (per arm)**
**N = 2 * n = 770 (total)**

### Recruitment

Patients will be recruited among those with breast DCIS who underwent BCS and visited the outpatient department of participating sites of the TBCC-ARO DCIS trial. In the current protocol, no advertising or inducements will be permitted and recruited. Patients will be randomized by the TBCC-developing “Clinical Study Information System” (CSIS) by logging clinicopathological information on their respective websites.

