### Statistics

#### Statistical methods for primary and secondary outcomes

In this study, patients who do not follow the protocol of their assigned treatment arm will not be analyzed. We will use the chi-square test, Student’s *t*-test, and Fisher’s exact test to compare the clinical characteristics between patients undergoing RT and those receiving low-dose tamoxifen. In this study, we will use the Kaplan–Meier method to estimate the time to IBTR (only breast area), ipsilateral regional recurrence of lymph nodes (including axillary, supraclavicular, or internal mammary lymph nodes), contralateral breast local recurrence, and distant metastases from the date of surgical excision. In addition, we will use this method to calculate overall survival, which will be measured from the date of surgical excision to the date of death from any cause or to the date of the last follow-up. Comparisons between the patients will be performed using the log-rank test. All statistical analyses will be carried out at a 5% significance level.

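### The 385 patients per arm contain no allowance for a 5% loss to follow-up, and the increase to 405 covers one 5% loss where the plan names two; the sample size also holds only if alpha is one-sided, which is not stated

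*Protocol article*

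**What the plan says.** The Sample size section gives 385 patients per group for 90% power at a 5% type I error and a 5-point margin, and continues: "this permits a loss of 5% of patients due to follow-up at 5 years". It refers to Table 2 for the method. Next it says that about 5% of patients will not tolerate low-dose tamoxifen and will receive RT, and on that ground "we estimate that 405 patients will be enrolled in the tamoxifen arm". The total becomes 810.

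Table 2 lists "α: type 1 error—> 0.05", "β: power—> 0.9" and "Assume that Tamoxifen = RT = 6" (per cent), with a margin of 5 percentage points in ipsilateral breast tumor recurrence (IBTR). It shows 385 per arm and 770 in total as the direct result of a one-line formula.

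The section on statistical methods for primary and secondary outcomes adds: "All statistical analyses will be carried out at a 5% significance level". None of these places says whether 5% is one-sided or two-sided.

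Two sections bear on whether intolerant patients count in the analysis. The statistical methods section leaves out patients who do not follow their assigned arm. The section on strategies to improve adherence keeps patients who refuse their assigned treatment in the intention-to-treat analysis.

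**The concern.** The plan names two separate 5% losses: loss to follow-up, and tamoxifen patients who cannot tolerate the drug. It says that the first is already inside the 385 and that the second explains the step to 405. If the 385 is the bare output of the formula, the first statement is false and only one of the two losses has been provided for. The stated 90% power would then belong to a sample slightly larger than the one the design expects to analyse.

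Sidedness matters more for the size of the effect. A figure that holds only at one-sided 5% should say so, because a reader who takes the 5% level as two-sided would judge the same 385 quite differently.

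**Working it through.** **Inputs.** From Table 2 and the Sample size section: 7-year IBTR of 6% in both arms, margin Δ = 0.05, power 90%, alpha 5% with sidedness not stated. Allocation is 1:1 (Abstract). The losses are 5% to follow-up and about 5% to tamoxifen intolerance. Table 2 does not define S²; I take S² = 2 × 0.06 × 0.94 = 0.1128, the unpooled variance for a difference of two proportions.

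**Reproducing 385.** N = (Zα + Zβ)² × S² / Δ².
- One-sided 5%: (1.645 + 1.2816)² × 0.1128 / 0.0025 = 386.4, rounded up to 387.
- The same with z rounded to 1.64 and 1.28: 2.92² × 0.1128 / 0.0025 = 384.7, that is 385.
- One-sided 2.5% (two-sided 5%): 474.1, rounded up to 475. This does not give 385.

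So 385 is reproduced at one-sided 5% with no loss term. For 385 to contain a 5% loss, the evaluable number would have to be 385 × 0.95 = 366. None of the variants tried at the stated 6%, 5 points, 90% and 5% gives 366.

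**The step to 405.** 385 / 0.95 = 405.3, and 405 × 0.95 = 384.75. The increase is exactly one 5% loss.

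**What is left to analyse.** Intolerance can occur only in the tamoxifen arm. If intolerant patients are left out and those lost to follow-up are treated as fully lost:
- RT: 405 × 0.95 = 384.75, about 385.
- Tamoxifen: 405 × 0.95 × 0.95 = 365.5, about 366.

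If intolerant patients are kept under intention to treat, each arm has 405 × 0.95 = 384.75.

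**Power.** Power = Φ(Δ/SE − Zα), with SE² = 0.06 × 0.94 × (1/n_RT + 1/n_Tam). For 384.75 against 365.5, SE = 0.01735 and Δ/SE = 2.882. Then 2.882 − 1.645 = 1.237, and power is 89.2%.

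| Evaluable RT / tamoxifen | Power, one-sided 5% | Power, one-sided 2.5% |
|---|---|---|
| 385 / 385 (no loss) | 89.9% | 83.2% |
| 384.75 / 384.75 (from 405, follow-up loss only) | 89.9% | 83.2% |
| 384.75 / 365.5 (from 405, both losses) | 89.2% | 82.2% |

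**The case against.** The strongest reply is that the effect is negligible. At one-sided 5%, the only reading that reproduces 385, power after both stated losses is 89.2%, less than one point below target. Even that is pessimistic. The plan uses Kaplan–Meier estimates, so a patient lost at 5 years still contributes the time observed. If intolerant patients stay in an intention-to-treat analysis, 405 leaves the planned 385 per arm; and under the plan's assumption of 6% in both arms, their move to RT does not change the expected rate. All of this stands. It limits the size of the point, but it does not make the sentence about 385 correct: Table 2 has no loss term.

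A reader might go further in three ways that the document does not support.

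- **That 854 patients are needed (385/0.95² = 427 per arm), a shortfall of 44.** This charges tamoxifen intolerance to the RT arm, where it cannot occur. With the losses placed where the plan puts them, matching the precision of 385 per arm takes (385/2) × (1/0.95 + 1/0.9025) = 416 per arm, or 832 in all.
- **That 20% of patients may be missing from the analysis.** The words "If at least 80% of case report forms are returned" refer to form return 5 years after starting treatment, and follow a sentence on the maturity of the data. They do not say that a fifth of patients will lack a 7-year outcome, so no power figure can be built on them.
- **That the trial is underpowered because 5% is two-sided.** Table 2 writes Zα, and 385 fits only the one-sided reading. The two-sided figures are conditional. What the document supports is that sidedness is not stated.

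**Conclusion.** The statement that 385 per arm permits a 5% loss to follow-up is wrong. By the plan's own formula, 385 is the evaluable number before any loss, and only at one-sided 5%. The increase to 405 covers one 5% loss, and the text assigns it to tamoxifen intolerance.

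At one-sided 5%, the cost in power is under one point: about 89% against the stated 90% if intolerant patients are excluded, and about 90% if they are kept. This assumes 6% in both arms, a simple comparison of proportions, and patients lost to follow-up counted as fully lost. It is not a failure of the design, and it does not by itself call for more patients.

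Two matters remain open in the text. The sidedness of alpha separates about 89% from about 82% power after both losses. Whether the second 5% is a loss at all depends on which of the two conflicting analysis rules applies.

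**What to change.** Keep 810 patients and change the text:

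1. In the Sample size section and Table 2, describe 385 per arm as the evaluable number before any loss, and delete the claim that it permits a 5% loss.
2. State that 405 per arm, after the follow-up loss in both arms and the intolerance loss in the tamoxifen arm, leaves about 385 RT and 366 tamoxifen patients and about 89% power.
3. State that alpha is one-sided 5% for the non-inferiority comparison. If a two-sided 5% interval is meant, say so and give power as about 82% after both losses.
4. Reconcile the statistical methods section with the section on adherence as to whether patients who stop tamoxifen are analysed. If they are kept, say that 405 covers the follow-up loss only. Keeping them costs no patients but dilutes any true difference between the arms, which the sample-size formula does not show.

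The cost is a few sentences and a slightly less favourable power figure. The Trial status section reports 36 patients enrolled by December 2022, so at that date the correction would have come early in recruitment.

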**α: type 1 error—> 0.05**
**β: power—> 0.9**
**Assume (no-RT) low risk IBTR: 6%**
**Assume that Tamoxifen = RT = 6%**
**Assume a margin (IBTR difference: 5%)**
**N = (Z**_**α**_** + Z**_**β**_**)**^**2**^**xS**^**2**^**/Δ**^**2**^ = **385 (per arm)**
**N = 2 * n = 770 (total)**

### Recruitment

Patients will be recruited among those with breast DCIS who underwent BCS and visited the outpatient department of participating sites of the TBCC-ARO DCIS trial. In the current protocol, no advertising or inducements will be permitted and recruited. Patients will be randomized by the TBCC-developing “Clinical Study Information System” (CSIS) by logging clinicopathological information on their respective websites.

### Assignment of interventions: allocation

#### Sequence generation

When patients meet the criteria of the current study, they will be stratified into different groups based on the pathological characteristics of their post-BCS tumor specimens (tumor size: ≤ 1 cm vs. > 1 cm; margin width: 3– < 10 mm vs. ≥ 10 mm) before randomization.

#### Concealment mechanism

In this study, randomization of patients with DCIS will be performed using the randomization module found in the CSIS website of the TBCC-ARO DCIS trial. The TBCC-ARO DCIS central site will be allocated a concealment of randomization.

#### Implementation

In this study, information on adjuvant RT and low-dose tamoxifen following BCS after randomization will be provided to participants who meet the inclusion criteria at the outpatient clinic. When written informed consent is obtained from participants, the participating investigators will introduce information on patients’ clinicopathological characteristics to the CSIS website of the TBCC-ARO trial via a secured module. Furthermore, each patient will receive a code number, and they will be randomized to the RT or low-dose tamoxifen arms after successful registration.

### Assignment of interventions: determining who will be blinded

The current protocol of the TBCC-DCIS trial is an international, open-label, randomized, non-inferiority trial. Therefore, no blinding is planned.

### Procedure for unblinding if needed

Because this is an open-label, randomized, non-inferiority trial, methods for blinding are not indicated.

### Data collection and management

#### Plans for assessment and collection of outcomes

After randomization, all patients will undergo annual mammography, hemogram, and biochemistry examinations every 6 months or every 12 months, for a total of 10 years (Table 1). The toxicity of RT will be assessed during RT or after its completion, while the toxicity of tamoxifen will be assessed after completion of its administration. Ipsilateral recurrence, contralateral recurrence, and survival will be assessed after entering the clinical trial.

### Plans to promote participant retention and complete follow-up

#### Data management

When the current trial is ongoing, its data will be accessed by the Data Safety and Monitoring Committee (SMC) and Statisticians of TBCC-ARO. The principal investigator has full responsibility for the assessment of clinical data, which will be available for the principal investigator and co-investigators, if the clinical trial is finished. Clinical data, including name, contract information, subject number, informed consent, pertinent medical history, result of key parameters of trials, adverse events, recurrence, and clinical outcomes of participants, will be sent to the CSIS website of the TBCC-ARO trial, and these data and documents will be stored for 10 years after trial completion or according to the regulatory requirements.

### Statistics

#### Statistical methods for primary and secondary outcomes

In this study, patients who do not follow the protocol of their assigned treatment arm will not be analyzed. We will use the chi-square test, Student’s *t*-test, and Fisher’s exact test to compare the clinical characteristics between patients undergoing RT and those receiving low-dose tamoxifen. In this study, we will use the Kaplan–Meier method to estimate the time to IBTR (only breast area), ipsilateral regional recurrence of lymph nodes (including axillary, supraclavicular, or internal mammary lymph nodes), contralateral breast local recurrence, and distant metastases from the date of surgical excision. In addition, we will use this method to calculate overall survival, which will be measured from the date of surgical excision to the date of death from any cause or to the date of the last follow-up. Comparisons between the patients will be performed using the log-rank test. All statistical analyses will be carried out at a 5% significance level.

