The randomized trial UK/ANZ (UK, Australia, and New Zealand) DCIS trial, which enrolled breast DCIS patients irrespective of low-risk or high-risk characteristics, showed that among patients who underwent BCS alone, administration of tamoxifen (20 mg/day for 5 years) significantly reduced ipsilateral (Hazard ratio [HR], 0.77; 95% confidence interval [CI], 0.59–0.98; *P* = 0.04) and contralateral breast events (HR, 0.27; 95% CI, 0.12–0.59; *P* = 0.001). However, the benefit of tamoxifen in reducing ipsilateral breast events (HR, 0.93; 95% CI, 0.50–1.75; *P* = 0.8) was not observed in the BCS plus RT group [8]. These findings suggest that the addition of tamoxifen after RT may not reduce IBTR in breast DCIS patients who had low-risk characteristics, like in cohort 1 of the ECOG E5194 trial. However, the association between IBTR and estrogen receptor (ER) status in tumors of patients with DCIS who entered the aforementioned trials was not assessed [4–6, 8].

Among 732 patients (41%) with breast DCIS who received tamoxifen from the original National Surgical Adjuvant Breast and Bowel Project B-24 population, in which ER-positive tumors were 76%, Allred et al. showed that tamoxifen administration significantly diminished ipsilateral and contralateral recurrent breast events in those with ER-positive tumors, but did not impede recurrent events in those with ER-negative tumors [9]. In addition, we observed that among breast DCIS patients who underwent BCS alone, age < 40 years and negative ER status in tumors were two prognostic factors for increasing IBTR [7]. Our study also revealed that, even among breast DCIS patients who had pathological features similar to those in cohort 1 of the ECOG E519 trial, ER-negative status was associated with a trend of higher 7-year IBTR (8% vs. 5%, *P* = 0.69) [7].

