### Interim analyses

We will perform interim analyses if the 5-year IBTR is > 5% in patients who received only low-dose tamoxifen or only underwent RT; furthermore, we will discontinue this non-inferiority trial according to the assumption that the cumulative incidence of IBTR in the experimental (tamoxifen) or control groups (RT) was 6% at 7 years.

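### Non-inferiority is framed on 7-year cumulative incidence of IBTR, but the planned analysis is Kaplan-Meier with deaths censored and a log-rank test, which neither estimates that quantity nor tests the 5-point margin (minor)

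*Protocol article*

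**What the plan says.** The Sample size section puts the trial question as whether low-dose tamoxifen is "not inferior in decreasing the cumulative incidence of IBTR when compared with the prescription of RT". It assumes 6% at 7 years on radiotherapy and no more than 6% on tamoxifen. Table 2 adds a margin of 5 points on the IBTR difference and 385 patients per arm. The Interim analyses section uses the same quantity: "the cumulative incidence of IBTR in the experimental (tamoxifen) or control groups (RT) was 6% at 7 years".

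The section on statistical methods for primary and secondary outcomes names a different tool: "we will use the Kaplan–Meier method to estimate the time to IBTR", with regional lymph node recurrence listed next, followed by "contralateral breast local recurrence, and distant metastases from the date of surgical excision". Death from any cause is an event only in the definition of overall survival. For inference the section offers one sentence, "Comparisons between the patients will be performed using the log-rank test", at a 5% significance level.

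The Outcomes section and the abstract give a broader primary endpoint than the one used for sizing: "Our primary objective is to observe breast tumor recurrence, including ipsilateral, regional, contralateral, and distant recurrences of breast cancer".

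**The concern.** A Kaplan-Meier curve for one recurrence type has to treat a death without that recurrence as censored. Its complement is the risk in a hypothetical population in which nobody dies first. Cumulative incidence is the proportion who actually have the recurrence by 7 years, and it is never larger. The article therefore names one quantity as its target and another as its estimate.

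The test has a similar problem. A log-rank test takes equal hazards over the whole of follow-up as its null hypothesis. It contains no margin and no 7-year time point, so neither a significant nor a non-significant result answers whether the 7-year difference is below 5 points.

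At stake is whether the reported figure is the one that the 6% and 5-point values refer to, and whether the planned comparison can support a non-inferiority claim.

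**Working it through.** **1. What the sample size targets.** Table 2 gives N = (Zα + Zβ)² × S² / Δ². It does not define S², so I take the binomial form S² = 2 × 0.06 × 0.94 = 0.1128, with Δ = 0.05 and power 90%.

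- One-sided 5%: (1.645 + 1.282)² = 8.564, and 8.564 × 0.1128 / 0.0025 = 386.4, so 387 per arm. The article states 385.
- One-sided 2.5%: 475 per arm, which does not reproduce the article's figure.

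The stated size is thus that of a comparison of two 7-year proportions on the absolute difference scale. Changing the estimator leaves it as it is.

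**2. Kaplan-Meier against cumulative incidence in one arm.** I assume constant hazards over t = 7 years, h1 for IBTR and h2 for death without IBTR.

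- One minus Kaplan-Meier = 1 − exp(−h1·t)
- Cumulative incidence = h1/(h1 + h2) × [1 − exp(−(h1 + h2)·t)]

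A Kaplan-Meier value of 6% gives h1·t = −ln(0.94) = 0.0619. With 5% deaths, h2·t = −ln(0.95) = 0.0513. Then 0.0619/0.1132 × (1 − 0.94 × 0.95) = 0.5468 × 0.107 = 5.85%.

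| Assumed 7-year death risk | One minus Kaplan-Meier | Cumulative incidence | Excess (points) |
|---|---|---|---|
| 2% | 6.00% | 5.94% | 0.06 |
| 4% | 6.00% | 5.88% | 0.12 |
| 5% | 6.00% | 5.85% | 0.15 |
| 10% | 6.00% | 5.70% | 0.30 |

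The death risks are assumptions, since the article gives none.

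**3. Effect on the difference.** With equal IBTR rates and equal death rates, the excess cancels. At the margin (Kaplan-Meier 11% against 6%, difference 5.0 points), 5% deaths in both arms give 10.73% − 5.85% = 4.88 points. Deaths of 3%, 8% and 15% give 4.93, 4.80 and 4.63. Under these assumptions, censoring deaths makes the difference look slightly larger, which is conservative for a non-inferiority claim.

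**4. Set against sampling error.** With 385 per arm at 6%, the standard error of the difference is √(0.1128/385) = 1.71 points. The one-sided 95% half-width is 1.645 × 1.71 = 2.8 points. An excess of 0.15 points in one arm is under a tenth of that standard error.

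**5. Log-rank against the margin.** Suppose the observed rates are 6% on radiotherapy and 8.5% on tamoxifen, halfway to the margin. The standard error is √[(0.06 × 0.94 + 0.085 × 0.915)/385] = 1.87 points, so z = 2.5/1.87 = 1.34. A test of equality is not significant at 5% (I use the binomial z as a stand-in for the log-rank). The one-sided 95% upper bound is 2.5 + 1.645 × 1.87 = 5.6 points, above the margin. A non-significant test would therefore sit beside data that do not show non-inferiority.

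**The case against.** **The effect is too small to matter.** For the estimator alone this largely stands. The exclusion of recent other neoplasms and of significant cardiac disease points to the low end of the death range, where the excess is about 0.1 points per arm. At the margin the direction is conservative.

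**Cumulative incidence is loose oncology usage.** The Sample size section moves between rate, incidence and cumulative incidence, so the term may not have been chosen as a competing-risks estimand. That is fair. But a 7-year absolute risk with a 5-point margin is still what was sized, and a log-rank test does not address it under any reading of the term.

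**The analysis plan may settle it.** Silence in the article would be no finding. Here the article names the estimator and the test. An analysis plan that follows it inherits the mismatch, and one that does not departs from it.

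**A stronger reading is tempting.** The Background cites "contralateral breast events (HR, 0.27; 95% CI, 0.12–0.59" for tamoxifen, so a reader might infer that contralateral events are censored unequally between arms and tilt the comparison. The article does not support this:

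- No section says that follow-up for IBTR stops at another recurrence. Each event type is timed from surgery, and the data collection section has all patients under annual mammography for 10 years, which reads more naturally as continued follow-up.
- The cited hazard ratio is for 20 mg/day against none after surgery alone, not 5 mg/day against radiotherapy. The article also reports fewer contralateral events with 5 mg against observation, so unequal contralateral rates are plausible, but that is not a censoring rule.
- Under the composite endpoint in the Outcomes section, a contralateral recurrence is itself an event.
- Even if such events were censored, the shift would be about 0.07 to 0.21 points under assumed contralateral risks of 5% to 10% on radiotherapy and 1.6% to 3.5% on tamoxifen, with 3% to 8% deaths.

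**Conclusion.** The mismatch is real and minor. The article names the 7-year cumulative incidence of IBTR and plans an estimator that censors deaths. The overstatement is about 0.06 to 0.30 points per arm at a 6% rate, given constant hazards and assumed 7-year death risks of 2% to 10%. That is small against the 5-point margin and unlikely by itself to alter the conclusion, and the sample size is unaffected. Death is the only competing event that the article establishes, and an unequal bias from contralateral events is not shown.

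The log-rank test stays valid for comparing cause-specific hazards, but it does not test a 5-point difference at 7 years. This is the more useful reason to revise the text.

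**What to change.** In the section on statistical methods for primary and secondary outcomes:

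- Estimate 7-year IBTR, and each other recurrence type, by arm with the Aalen-Johansen cumulative incidence function, with death as a competing event.
- State that IBTR counts whether or not another recurrence came first.
- Judge non-inferiority by the confidence bound for the between-arm difference in 7-year cumulative incidence against 5 points. The log-rank test can remain as a supporting comparison.
- If the composite recurrence endpoint of the abstract and Outcomes section is the primary one, apply the same method to it, again with death as the competing event.
- Keep Kaplan-Meier for overall survival.

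The cost is a few sentences and standard software. Ipsilateral recurrence, contralateral recurrence and survival are already to be assessed, so no new data are needed. The Trial status section reports 36 patients enrolled by December 2022 against a target of 810, so the change can be made well before the final analysis.
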